## Abstract

**Background:**

Non-specific chronic low back pain (NCLBP) is a major public health and global socioeconomic burden with a variety of symptoms such as gait abnormality. Trunk stiffness and deep trunk muscles dysfunction known as guarding mechanism in gait are factors leading to abnormal movement pattern of the spine. Anterior load carriage task during gait is also challenged the trunk stability and its movement pattern. It will be therefore of interest to examine the effect of a Core Stabilization Training Program (CSTP) on the trunk and pelvis kinematics including variability and peak displacement during gait with and without load in NCLBP patients.

**Methods:**

Patients with NCLBP will participate in a program containing 16 sessions of CSTP and perceived pain, disability and kinematic will be evaluated with 100 mm visual analog scale (VAS), Oswestry Disability Index (ODI) and motion analyzing system respectively before and after the intervention. Participants will be asked to walk with self-selected comfortable speed for 3 times without load and 3 times with caring a load with hands.

**Discussions:**

We will quantify the effectiveness of CSTP on the kinematic of trunk, lumbar and pelvis during gait. Comparing the kinematic pattern and movement variability using CV_o_ and CV_p_ can contribute to better understand the motor control strategy and movement pattern of the spine during an anterior load carriage task between patients with NCLBP and healthy.

**Trial registration:**

IRCT number: IRCT2016080829264N1; pre-result.

## Background

Chronic Low back pain (CLBP) is one of the most prevalent problems up to 84% [1, 2]. Despite its prevalence, no specific causes can be found for almost 85% of the CLBP cases [3]. Therefore, this type of low back pain, named non-specific chronic low back pain (NCLBP), acknowledged multifactorial conditions with various dysfunctions, such as gait abnormality [4–6]. Gait is an activity that is repeated frequently throughout the day. The trunk and lumbar spine, however help drive in human bipedal gait [7]. It has been suggested that deficiencies in motor control during gait following LBP produce repeated and prolonged stresses on the spine [6, 8]. Various studies have reported that patients with CLBP alter their movement pattern and control strategy to avoid painful motion [9, 10]. In a recent review, authors have reported that it is unlikely that gait is independently causative of LBP [11], thus the gait observed in CLBP might be considered a symptom instead [6, 12].

In quantitative analysis of spine movement, the peak displacement, velocity and, acceleration as an angular measurement, and the variability of movements have been measured upon three planes including sagittal, frontal and transverse during gait. The movement variability is more affected by 1) the reliability and errors of measurement, 2) repeatability of the motor performance [13]. It also contains information about how movement changes overtime [14]. Gait studies in healthy subjects had shown relatively low variability of movement in the lumbar spine during treadmill walking [15]. Also, people with CLBP displayed less lumbar displacement [6, 8] and higher lumbar movement variability during treadmill walking [6]. CLBP also exhibited more frontal plane coordination variability and more rigid transverse plane coordination variability of the thorax – pelvis compared to healthy in treadmill walking [9]. However, more rigid sagittal and transverse planes coordination variability obtained from studies of CLBP in over-ground walking compared to healthy subjects [16–18]. Therefore, subjects with CLBP exhibit more in phase trunk – pelvis movement coordination and lower repeatability of lumbar spine movement patterns during gait, revealed higher noise and error in the motor performance that supports the “guarded gait” mechanism [10, 16–20]. Gombatto et al. also evaluated the lumbar spine kinematics including displacement in the different movement-based subgroups of CLBP. Although people with CLBP displayed significantly less overall lumbar rotation than controls, they did not show any significant differences in lumbar kinematics during gait among subgroups [8].

Anterior load carriage during walking is frequently the main task in some industries and individuals in their daily activities that repeated throughout the life challenging the spinal stability and trunk-pelvis movement pattern [21]. It has been suggested that loading conditions with high repetition and frequency can cause to muscular hyper-activity and possible tissue failure and pain in lumbar spine [22, 23]. Anterior load carriage causes to increase of the trunk muscle activity and compressive load on the spine that is reported to be a factor of abnormal movement pattern and can cause to development of LBP [21, 24]. Transverse trunk and pelvis coordination is essential and can be affected during gait-including anterior load carriage in various speeds [21]. Evidence demonstrated that patients with CLBP who have reduced stability exhibited more anti-phase trunk and pelvis coordination pattern during gait associated with an anterior load carriage compared to healthy subjects [21].

Previous studies have demonstrated that an association exists between CLBP and dysfunction in the deep trunk muscle activation pattern [25, 26]. The deep muscles such as transverse abdominis (TrA) and multifidus have large contributions to control the intervertebral movement via the proper timing and coordinated activity during a task irrespective to the direction of force [26–29]. There is evidence that the TrA exhibits a reduced amplitude and delay in activation during repetitive trunk and limb movement such as gait [26, 27]. Multifidus and deep paraspinal muscles show similar changes in activity during functional task as well as loading activity in CLBP [26, 29]. It appears that the abnormal kinematic pattern seen in CLBP during gait combined with increased superficial muscles activity such as erector spinae and rectus abdominis [19], contributing to a poor motor control. Other studies revealed an increased uncoordinated activity of lumbar multifidus, longissimus and lateral abdominal muscles [28, 30, 31] supporting the guarding mechanism during gait. Although, the increase in the superficial trunk muscle activity can prevent lumbar spine buckling and increases the lumbar spine stiffness [28], it is also associated with increased compressive loading of the spine which has been considered as a risk factor for spinal pain and degeneration [28, 32].

According to the European guidelines for the management of CLBP, exercise therapy has strong evidence for the reduction of pain and disability and return to work [2]. However, there is no evidence favoring one form of exercise therapy including “stabilization exercise” for the treatment of LBP in the current guidelines. Local muscle training (core training) has developed as an exercise regimen focusing on motor control and muscle capacity can reduce the pain and disability, it also improves lumbo-pelvic stability (LPS) and restores the function of the spine in daily tasks in CLBP [27, 28, 33–36]. These studies recommended that core training exercises focusing on the TrA and multifidus muscles can restore the LPS and can help to recovery from injury enhancing the spine (the lumbar and thoracic) and pelvis as well as the lower limb performance in static and dynamic functional tasks [26, 27, 37]. Based on previous studies, the size of multifidus and TrA muscles is recovered during tasks including the active straight leg rise, abdominal drawing maneuver, hook lying and standing with a load after a period of core training [38–40]. It is also improved the electromyographic activity of these muscles during flexion-extension task [41, 42], lumbar lordosis [43] and motor cortex representation area of the TrA and multifidus in the brain [44]. Data about the effect of exercise therapy on spine kinematics during gait is very limited. However, Steele et al. evaluated the effect of isolated lumbar extension exercise on lumbar kinematics during gait in CLBP [45]. They reported that the sagittal plane pattern variability decreased after this program. However, the mean displacement in three planes and the pattern variability in the transverse and frontal planes remained unaltered after the isolated lumbar extension exercise [45]. Carpes et al. in a pilot study investigated the effect of a program of strength and endurance training on the spine kinematics. They reported that the trunk rotation and right pelvic tilt increased and the lumbar lordosis decreased after this program [43].

It is possible that the trunk stiffness, and altered lumbar and trunk kinematics including higher movement variability and lower displacement are a manifestation of commonly associated core muscles dysfunction [9]. Core muscles dysfunction can contribute to the poor motor control during gait that may result in compensatory trunk stiffness [19]. To the best of authors’ knowledge, the effect of isolated core training program on the between-trial variability and displacement of the trunk has not been investigated yet. On the other hand, the effect of an anterior load carriage task that is disruptive for LPS to alter the trunk movement pattern has not evaluated in previous studies. Thereby, previous studies have failed to reveal the effect of specific core training program on the lumbar, and trunk kinematics including between-trial variability as well as peak displacement during gait including anterior load carriage.

The study hypotheses are as follows:NCLBP group shows a lower between-trial variability and peak displacement of the trunk movement relative to the pelvis in the sagittal, frontal and transverse planes during gait with and without load compared to healthy.NCLBP group shows a lower between-trial variability and peak displacement of the lumbar movement relative to the pelvis in the sagittal, frontal and transverse planes during gait with and without load compared to healthy.Core stabilization exercise therapy increases the between-trial variability and peak displacement of the trunk relative to the pelvis in the sagittal, frontal and transverse planes during gait with and without load in NCLBP.Core stabilization exercise therapy increases the between-trial variability and peak displacement of the lumbar relative to the pelvis in the sagittal, frontal and transverse planes during gait with and without load in NCLBP.

## Methods

### Study aims

The primary aim of this study is to evaluate the effect of 16-sessions core stabilization program on pain, disability and the spine kinematics while subjects walking with self-selected speed in subjects with NCLBP and comparison with healthy subjects.

### Study design

This study will be conducted at the motion analyzing laboratory of the rehabilitation faculty of Iran University of medical sciences (IUMS). The study is a clinical trial designed to investigate the effect of 16 sessions core stabilization exercise on the trunk and lumbar kinematics relative to the pelvis with and without load during gait and compared with a healthy participants matched group.

### Approval of study protocol

This study has been approved by Ethical committee at Iran University of Medical Sciences (Ethical Approval Number: IR.IUMS.REC 1395.9211342205), (IRCT number: IRCT2016080829264N1).

### Participants

As there is no previous work to estimate the effect size for the kinematic variables considered here, we will conduct a pilot study to compute and estimate the effect size. Then, using power analysis, the required sample size with a power of 0.8 and an α of 0.05 will be determined. Assuming a large effect size, we anticipate recruiting 30 participants (15 in each group) for the study. Both males and females will be recruited in the study. The enrolment will be continued to reach the required sample size. Table 1 summarizes the inclusion and exclusion criteria for the CLBP group. Since the lumbar and trunk kinematics were not different during gait in the movement-based subgroups of NCLBP in a recent study [8], therefore in this study we will examined the NCLBP group regardless of their movement-based classification. Fifteen Healthy non-athlete subjects with no previous history of LBP will be included. Each healthy subject will be matched to a subject with LBP based on the age, sex, height, weight and BMI. In this group, subjects with a history of fracture, trauma and, pain of any other joints in the past also will be excluded from the study. In both groups participants will be excluded from the study if they have BMI higher than 30. Harsted et al. reported that CLBP with a BMI higher than 30 exhibited less variable and lower mean frontal plane range of motion compared to participants with a BMI below 30 [46]. However, less variability of movement of the trunk in this group is generally dependent to larger body mass instead of spine function [46].

**Table 1 Tab1:** Inclusion and exclusion criteria for the CLBP

Inclusion criteria	Exclusion criteria
The age range of 18–45 years. Current nonspecific Low back pain Lasting more than 12 weeks.	Sciatic nerve root involvement Pain radiating to the leg below the knee Paresthesia in the feet Motor deficits in the lower extremity muscles Acute spinal disc herniation Previous surgery or fractures in lumbar spine or Other bonny structures Neurologic disorders Recent any significant trauma to the musculoskeletal system such as bonny, muscular, ligamentous and soft tissue structures in the upper, lower extremity, head, neck and trunk that might interfere with gait [10, 16] Any clinical conditions such as musculoskeletal, neurological, cardiac or pulmonary or symptom that might interfere with gait [10, 63] Osteoarthritis of the knee and hip [10] Recent unexplained weight loss BMI above 30 kg/m^2^ [46] (see the participants section) Any medical condition which have contraindications to exercise therapy including acute (not reoccurring) low back injury occurring within the last 12 weeks, current tension sign, pregnancy, inflammatory disease, sever osteoporosis, arthritis and bone disease [37, 45, 64]

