#### Statistical analysis

Data will be analyzed using SPSS version 21 (SPSS Inc., Chicago, IL) software. The normal distribution of data will be analyzed by a Kolmogorov-Smirnov Z test. If the distribution is normal, the outcomes of the studied measurements will be evaluated the absolute change from pre- to post- for VAS, ODI and the kinematic variables using a paired T-test in CLBP group. To determine homogeneity of variances (i.e., variances approximately equal across groups), Levene’s test will be employed. In addition, to evaluate the kinematics variables between CLBP and healthy group, an independent samples T-test will be used to reveal any difference between two groups. A non-parametric test will be used if the data are not normally distributed to compare across two groups (healthy and CLBP) using a Mann Whitney U exact test and, a Wilcoxon signed rank exact test will be used to compare of the variables in pre and post intervention in CLBP. A *p*-value of less than 0.05 will be considered statistically significant. According to the Raymond et al. study [59] minimal change that can be considered with perceived pain questionnaire and ODI in low back pain are clinically useful for interpretation of results. Results of VAS and ODI will be compared with range of minimal important change (MIC) value for pain (15.0–20.0 points) and ODI (10.0–12.0 points) [59].

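### At a conventional large effect, 15 per group meets the 80% power target only for the paired pre-post test; the planned patient-versus-healthy t-test has about 56%

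*Protocol article*

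**What the plan says.** The protocol article, Participants, says that a pilot will estimate the effect size and that afterwards, "using power analysis, the required sample size with a power of 0.8 and an α of 0.05 will be determined". The next sentence gives the only sample size in the document: "Assuming a large effect size, we anticipate recruiting 30 participants (15 in each group) for the study". The section then says that enrolment will go on until the required size is reached, and a few lines later, without qualification: "Fifteen Healthy non-athlete subjects with no previous history of LBP will be included".

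Statistical analysis plans two kinds of test. Change from before to after training in the patients is tested with a paired t-test. For the kinematic comparison with healthy subjects, "an independent samples T-test will be used to reveal any difference between two groups". Rank tests replace both if the data are not normal. The significance rule is a p-"value of less than 0.05 will be considered statistically significant", and sidedness is not stated.

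Of the four hypotheses at the end of the Background, 1 and 2 compare patients with healthy subjects and so rest on the independent test. Hypotheses 3 and 4 concern change with training and rest on the paired test. Study aims includes the comparison with healthy subjects in the primary aim.

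**The concern.** One unspecified large effect and one group size stand beside one power target, but the two planned tests need very different numbers. A paired test on n people and an independent test on n + n people do not have the same power at the same standardised effect. The figure of 15 looks like the answer for the paired test, carried over to each group.

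Hypotheses 1 and 2, half of the hypotheses and part of the primary aim, are at stake. A reader who takes 15 + 15 as the size that goes with 0.8 power could read a non-significant patient-healthy result as evidence that gait does not differ. At a conventional large effect the planned test would miss such a difference more than four times in ten.

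**Working it through.** **Inputs from the protocol article**
- Target power 0.8 and α 0.05 (Participants).
- 15 patients and 15 healthy subjects (Participants).
- Paired t-test within patients; independent-samples t-test between groups (Statistical analysis).

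**Assumptions**
- Large = 0.8, the usual convention. The document gives no number, so a range is shown.
- Two-sided testing. One-sided results are shown because the hypotheses are directional.
- No multiplicity adjustment, as none is stated.

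**Method.** Power comes from the noncentral t distribution with df degrees of freedom and noncentrality λ: the probability that |T| exceeds the upper 2.5% point of the central t.

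**Step 1: reproduce the 15.** Paired test, with dz = mean change / SD of change:
- df = n − 1 = 14; λ = dz·√n = 0.8 × √15 = 3.10; power = 0.821.
- With n = 14, power = 0.790. The solved n is 14.3, which rounds up to 15.
- With n = 15, 80% power is reached at dz = 0.78.

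So 15 is the paired-test requirement at 0.8.

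**Step 2: the independent test at 15 + 15.** Here d = mean difference / between-person SD:
- df = 2n − 2 = 28; λ = d·√(n/2) = 0.8 × √7.5 = 2.19; power = 0.562.
- One-sided: 0.689. Mann-Whitney, approximated with relative efficiency 0.955: about 0.54.

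| d | Power, 15 + 15, two-sided |
|---|---|
| 0.8 | 0.56 |
| 0.9 | 0.66 |
| 1.0 | 0.75 |
| 1.1 | 0.83 |
| 1.2 | 0.89 |

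80% power is reached at d = 1.06 (one-sided 0.93).

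**Step 3: the size needed at d = 0.8.** The solved n is 25.5 per group: 25 gives 0.791 and 26 gives 0.807. That is 26 per group, 2 × 26 = 52 in total, against 30 anticipated. The normal approximation gives 25 per group, and a one-sided t-test 21. No unpaired variant gives 15.

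**Step 4: are the two effects the same quantity?** With equal SDs and correlation ρ between the paired measurements, dz = d / √(2(1 − ρ)). The two coincide only when 2(1 − ρ) = 1, that is at ρ = 0.5. A single unlabelled large effect therefore does not size both tests.

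**The case against.** The strongest reply is that no power is claimed for 15 + 15. The 0.8 is the target for a size still to be worked out after a pilot, 30 is only anticipated, and enrolment continues to the required number. This stands. A reader might infer that the protocol states 80% power for the patient-healthy test and is simply wrong; the text does not say that. What remains is that 15 + 15 is the only size given, directly after the power target and tied to a large effect, with neither the effect nor the test specified.

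Second, large has no number, so 56% is conditional on d = 0.8. This also stands. However, 80% needs d of about 1.06, roughly a third above the convention (1.06 / 0.8 = 1.325), and nothing in the document supports a value that high.

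Third, healthy subjects are matched individually, which could recover power. Analysed as pairs at d = 0.8, 15 pairs would have 53%, 68%, 82% and 90% power at within-pair correlations of 0, 0.3, 0.5 and 0.6. That analysis is not planned; the stated test is the independent one.

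Fourth, a reader might see a contradiction between "As there is no previous work to estimate the effect size for the kinematic variables considered here" and the Background, which reports an exercise study of lumbar gait kinematics ("They reported that the sagittal plane pattern variability decreased after this program") and comparisons of patients with healthy people. The overlap is only partial. That exercise study used isolated lumbar extension, and several of the comparisons were made on a treadmill or concern coordination variability. The gap claimed in the Background concerns core training, the trunk, and walking with an anterior load. The documents do not support striking the sentence out.

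**Conclusion.** The point holds in a conditional form. If large means 0.8 and tests are two-sided, the anticipated 15 per group meets the 0.8 target for the paired test behind hypotheses 3 and 4 (0.82). It falls short for the independent test behind hypotheses 1 and 2 (about 0.56, or 0.69 one-sided), which would need 26 per group. The shortfall disappears only if the true patient-healthy difference is about 1.06 SD or more. The arithmetic is not in dispute; the choice of 0.8 is an assumption.

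The fault is that one size is offered for an unquantified effect and an unnamed test, although the two planned tests differ this much. It is not a false power claim. Nor does it follow that the patient-healthy comparison should be demoted to secondary: Study aims places it in the primary aim.

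**What to change.** In Participants:

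1. State the numerical effect size meant by large, and whether it is d or dz.
2. Give the power for each test separately. Fifteen patients give 80% power for the paired test at dz of about 0.78. Fifteen per group give 80% power for the patient-healthy test only at d of about 1.06, and about 56% at d = 0.8 (two-sided, α 0.05).
3. Reconcile the flat statement that fifteen healthy subjects will be included with the rule that enrolment continues to the required size. Say which test that required size will be calculated for; for the independent test at d = 0.8 it would be 26 per group.

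In Statistical analysis, commit to reporting the patient-healthy differences with 95% confidence intervals, so that a non-significant result is not read as no difference.

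These are wording changes and do not in themselves alter recruitment. The cost is that the stated power for hypotheses 1 and 2 becomes less favourable.

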### Recruitment

The physiotherapist (RB) who is a doctoral candidate with more than 10 years of clinical experience will recruit participants in this study from the IUMS orthopedics and physiotherapy clinics who diagnosed with NCLBP. The physician will refer participants with CLBP to these clinics. In addition, CLBP will be identified and recruited by posters, emails and word of mouth from the university and the surrounding locality. Healthy Participants will be matched in age, gender, body mass index with no history of low back pain. Healthy participants will be recruited through advertisements on bulletin boards and verbal requests in the rehabilitation department at IUMS and surrounding locality.

